**Abstract**

**Background**: A wide range of psychiatric disorders are more prevalent in individuals with Type 2 Diabetes Mellitus (T2D) than in the general population. Most of the studies, so far, have focused on the coexistence of diabetes and depression, based on self-administered questionnaires developed specifically for psychiatric patients.

**Aim of the study:** To evaluate the prevalence of psychiatric disorders, in a sample of consecutive outpatient clinic attendees with T2D at the Diabetes Care Unit of the Fondazione Policlinico Universitario Agostino Gemelli IRCCS, UCSC, Rome, Italy (FPUAG) using a scale developed specifically for the screening of psychiatric diseases in internal medicine patients the PHQ.

**Inclusion Criteria:** Age between 18 and 85 aa, Diagnosis of T2D.

**Statistical Plan**: the achievement of the primary objective, assuming an expected prevalence of 37.5%, with an accuracy of 7% and a confidence level of 97% is guaranteed by a sample size of n = 184 patients.

**Data analysis:** the sample will be described through descriptive statistical techniques. The qualitative variables will be represented by tables of absolute and percentage frequencies. The quantity will be summarized through measurements of minimum, maximum, range, mean and standard deviation. Continuous variables will be checked for normality with Shapiro Wilk test.

**Date:** 08 August 2020

**Version:** 3

This study protocol has been designed and will be conducted in accordance with the principles enshrined in the Good Clinical Practice (GCP) guidelines as applicable and in compliance with the Declaration of Helsinki and current guidelines for observational studies.

Summary

[Synopsis 4](#_Toc18742526)

[Introduction and rationale](#_Toc18742527) 5

……………………………………………………………………………………………………………………………………………………………………….

[Study objectives 6](#_Toc18742528)

[Study design, duration and setting 6](#_Toc18742529)

[Materials and methods 7](#_Toc18742530)

[Inclusion criteria 7](#_Toc18742531)

[Exclusion criteria 7](#_Toc18742532)

[Study procedures 7](#_Toc18742533)

[Statistical considerations 8](#_Toc18742534)

[Sample size 8](#_Toc18742535)

[Data Analysis 8](#_Toc18742536)

[References 8](#_Toc18742537)

# Synopsis

| **Title** | Evaluation of the prevalence of the most common psychiatric disorders in patients with type 2 diabetes using the Patient Health Questionnaire: results of the cross-sectional “DIA2PSI” study. |
| --- | --- |
| **Acronym** | DIA2PSI |
| ***Protocol number*** | 0040703/20 |
| ***EudraCTNumber*** | [N/A](https://it.wikipedia.org/wiki/N/A) |
| ***NCT number (clinicaltrials.gov)*** | N/A |
| **Version** | 3 |
| **Date** | 08/08/2020 |
| **Place of the study** | Fondazione Policlinico Universitario Agostino Gemelli IRCCS, UCSC, Rome, Italy (FPUAG) |
| **PI and CoPI** | PI: [name] |
| **Study design** | Cross sectional study |
| **Blinding** | None |
| **Primary objective** | Evaluation of the prevalence of psychiatric disorders, in a sample of consecutive outpatient clinic attendees with T2D at the Diabetes mellitus Unit of the Fondazione Policlinico Universitario Agostino Gemelli IRCCS, UCSC, Rome, Italy (FPUAG) using a scale developed specifically for the screening of psychiatric diseases in general internal medicine patients, the PHQ. |
| **Secondary objective** | None |
| **Primary endpoint** | The primary objective will be achieved through the calculation of the prevalence of psychiatric disorders in patients with T2D. |
| **Secondary endpoint** | Organize a permanent psychiatric screening at the Diabetes Care Units of the FPUAG for patients with T2D, to initiate an integrated psychiatric-diabetic for people with T2D and who have a comorbid psychiatric disorder. |
| **Rational** | It is known that a wide range of psychiatric disorders have a higher prevalence in individuals with T2D than in the general population. However, so far, most studies have focused on the co-presence of T2D and depression based on self-administered questionnaires developed specifically for psychiatric patients. |
| **Inclusion criteria** | -Age between 18 and 85 aa  -Diagnosis of T2D according to the American Diabetes Association (ADA) |
| **Exclusion criteria** | -Diagnosis of Type 1 diabetes mellitus  -Inability to complete the survey tools because of cognitive difficulties  -To be very sick and unable to read and understand Italian  -Women who were pregnant or had given birth in the last 6 months were also excluded. |
| **Study procedures** | - fulfill an information form for each patient.  -Patients who agree to join the study will be requested to complete the Patient Health Questionnaire. |
| **Sample size** | the achievement of the primary objective, assuming an expected prevalence of 37.5%, with an accuracy of 7% and a confidence level of 97% is guaranteed by a sample size of n = 184 patients. The values taken into account are based on the few studies carried out and present in the literature which report a prevalence of psychiatric comorbidities of 37.5% in patients with T2D. |
| **Statistical analysis** | The patients included will be described in their clinical and demographic characteristics through descriptive statistics techniques. Continuous variables will be checked for normality with Shapiro Wilk test. Therefore, normally distributed data will be express as mean and standard deviation (SD), and non-normally with median and first and third quartiles (q1-q3). Dichotomous variables, categorical variables, and scores we will be express as numbers and percentages.  Primary outcome is the prevalence of common psychiatric disorders in patients with T2D assessed through the Patient Health Questionnaire. Moreover, to evaluate potential risk/protective factors associated with patients’ psychiatric disorders positivity, we will perform univariable logistic regression models. Therefore, for each factor, we will calculate the Odds Ratio (OR) with 95% Confidence Interval (CI) of being positive to PHQ. Statistical analyses will perform with Stata software, and statistical significance cut-off was set p<0.05. |

# Introduction and rationale

According to 2016 Istat data, there are over 3,2 million people with diabetes in Italy, 5.3% of the entire population, 16.5% among people over 65^1^ . The etiology of T2D is related to a diabetogenic lifestyle (excessive caloric intake, visceral and central obesity, and reduced physical activity). Although, according to the ADA guidelines, among the cornerstones of T2D therapy there is the increase of physical activity and healthy eating habits^2^, known and hypothetically feasible primary and secondary prevention interventions, it is estimated a continued increase in the obese/overweight population and people with T2D and in the years to come^3^. A wide range of psychiatric disorders have a higher prevalence in people with diabetes than in the general population^4,5^, but most studies present in the literature have evaluated the prevalence of psychiatric disorders in patients with both type 1 diabetes (T1D) and T2D, focusing mainly on the coexistence of depression and diabetes^6,7,8,9^ not considering other psychiatric disorders. In this study we will evaluate instead the prevalence of common psychiatric Disorders only in patients with T2D.

# Objectives of the study

The evaluation of the **prevalence** of common psychiatric disorders (not only depression) in a sample of consecutive outpatient clinic attendees with T2D at the Diabetes mellitus Unit of the Fondazione Policlinico Universitario Agostino Gemelli IRCCS, UCSC, Rome, Italy (FPUAG) using a scale developed specifically for the screening of psychiatric diseases in internal medicine patients the PHQ^10^; this tool, given the greater burden of somatic symptoms in internal medicine patients, is more suitable for identifying psychiatric disorders in this category of patients, than the scales developed for screening psychiatric disorders in psychiatric patients.

# Study design, duration and *setting*

Monocentric cross-sectional study. The study will take place at FPUAG, starting from October 2020. The recruitment and data collection period coincides. The study will last 1 year.

#

# Materials and methods

Patients aged between 18 and 85 years, diagnosed with T2D according to ADA^11^, belonging to the Diabetes Care Unit of the FPUAG will be recruited. The algorithm developed by the authors and supplied with the PHQ will be used for the coding of psychiatric diagnoses^10^. The PHQ is a self-administered questionnaire that allows to evaluate the presence of specific disorders: major depressive disorder, other depressive disorders, panic attack disorder, other anxiety disorders, bulimia nervosa, binge eating disorder, dependence, or alcohol abuse.

In this study all the sections, from 1-11, of the official Italian version of the PHQ will be used. The algorithm developed by the authors will be used to make the diagnosis with the PHQ^10^.

## Inclusion criteria

- Age between 18 and 85 aa

- Diagnosis of T2D according to the ADA

##

## Exclusion criteria

- Very sick patients unable to read in Italian were excluded

- Diagnosis of T1D

- Inability to complete the survey tools because of cognitive difficulties

- Be very sick and unable to read and understand Italian

- Women who were pregnant or had given birth in the last 6 months.

## Study procedures

Patients who agree to participate in the study will receive the PHQ test. Those who will test positive will be contacted for a psychiatric visit.

**Statistical considerations**

## Sample size

The achievement of the primary objective, i.e. the estimation of the prevalence of psychiatric diseases in patients suffering from T2D, assuming an expected prevalence of 37.5%, with an accuracy of 7% and a confidence level of 97% is guaranteed by a sample size equal to **N =** **184 patients** to which the PHQ test will be administered.

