## Data analysis

The sample will be described in its clinical and demographic characteristics through descriptive statistical techniques. Continuous variables had been checked for normality with Shapiro Wilk test. Therefore, normally distributed data were expressed as mean and standard deviation (SD), and non-normally with median and first and third quartiles (q1-q3). Dichotomous variables, categorical variables, and scores were expressed as numbers and percentages.

Primary outcome was the prevalence of common psychiatric disorders in patients with T2D assessed through the Patient Health Questionnaire. Moreover, to evaluate potential risk/protective factors associated with patients’ psychiatric disorders positivity, we performed univariable logistic regression models. Therefore, for each factor, we calculated the Odds Ratio (OR) with 95% Confidence Interval (CI) of being positive to PHQ. Statistical analyses were performed with Stata software, and statistical significance cut-off was set p<0.05.

**The primary objective** will be achieved through the calculation of the prevalence of common psychiatric diseases in patients with T2D.

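### 184 patients give ±7 points at 95% confidence, not at the stated 97%, so the only precision claim for the primary objective does not hold as written

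*Protocol*

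**What the plan says.** The Sample size section rests on three inputs. It plans "assuming an expected prevalence of 37.5" per cent, and it states that "an accuracy of 7% and a confidence level of 97% is guaranteed by a sample size equal to" 184 patients who will be given the PHQ. The Abstract (Statistical Plan) and the Synopsis (Sample size row) make the same claim: "with an accuracy of 7% and a confidence level of 97% is guaranteed by a sample size of n = 184 patients". The Synopsis adds that the planning prevalence comes from the few published studies, which "report a prevalence of psychiatric comorbidities of 37.5% in patients with T2D".

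The protocol gives no formula, sidedness, source population size or allowance for unusable questionnaires. The Synopsis lists no secondary objective. The only confidence level named in the Data analysis section is for the risk-factor odds ratios: "we calculated the Odds Ratio (OR) with 95% Confidence Interval (CI) of being positive to PHQ".

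**The concern.** Expected prevalence, margin, confidence level and sample size are tied together by one formula, so any three fix the fourth. Here the four do not fit: 184 is what the formula returns at 95%, while the text says 97%.

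Prevalence estimation is the sole objective, and this is the only precision the protocol promises for it, in the word guaranteed. The team cannot satisfy the sentence as it stands. If the prevalence is reported with a 97% interval, the margin will exceed 7 points at the planning prevalence. If it is reported with a 95% interval, the report departs from the only confidence level the protocol attaches to the estimate. A statistical analysis plan could not resolve this, because the statement is a numerical claim about what 184 patients deliver.

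**Working it through.** **Inputs, all from the Sample size section**
- Expected prevalence p = 0.375, so p(1−p) = 0.375 × 0.625 = 0.234375.
- Margin d = 0.07, read as ±7 percentage points, so d² = 0.0049.
- Stated confidence 97%. Sidedness is not given; two-sided is assumed, as is usual for the precision of an estimate.
- Stated N = 184.

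**Step 1. Which confidence level reproduces 184?** Using n = z²p(1−p)/d²:
- 95%, z = 1.95996: 3.84146 × 0.234375 / 0.0049 = 183.74, rounded up to **184**.
- 97%, z = 2.17009: 4.70929 × 0.234375 / 0.0049 = 225.25, rounded up to **226**.

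The stated N agrees exactly with 95%. At 97% it is short by 226 − 184 = 42 patients, which is 42/184 = 23% more than planned.

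**Step 2. What do 184 patients deliver?** The standard error is √(0.234375/184) = 0.03569.
- 95% half-width: 1.960 × 0.03569 = 0.06995, or ±7.00 points.
- 97% half-width: 2.170 × 0.03569 = 0.07745, or ±7.75 points.
- Confidence for ±7 points: 0.07/0.03569 = 1.961, which corresponds to 95.02% two-sided.

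**Step 3. Does another reading give 184 at 97%?**

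| Reading at 97% | n required |
|---|---|
| Wilson interval | 221 |
| Agresti-Coull interval | 222 |
| Clopper-Pearson interval | 237 |
| Normal approximation with continuity correction | 240 |
| p = 0.5 instead of 0.375 | 241 |
| 7% as the total width of the interval | 902 |
| 7% as relative precision | 1,602 |
| One-sided bound (z = 1.881) | 170 |

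None returns 184.

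**Step 4. Finite population correction.** With source population M, the required n is 225.25 / (1 + 224.25/M).
- M = 500: 155.5
- M = 1,000: 183.99, rounded up to 184
- M = 2,000: 202.5
- M = 5,000: 215.6

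The result rounds up to 184 only for M from about 972 to 1,000.

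**The case against.** The strongest counter-argument is the finite population correction. A source population of 1,000 is a round number, it gives 184 at 97%, and the study samples consecutive attendees of one unit over one year, so a finite source population is conceivable. If that is how N was obtained, the sentence would be correct on unstated premises. It remains possible, so how the error arose is an inference and the sponsor should be asked. It does not rescue the text as written. The protocol gives no population size and no correction, the match holds only in a narrow range of population sizes, and the objective concerns patients with type 2 diabetes rather than a closed list of about 1,000 people. The 95% reading needs no unstated input.

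A one-sided 97% bound would be met by 184, since it needs only 170. But that calculation does not produce 184, and accuracy of a prevalence ordinarily means a margin on both sides.

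The 95% level in the Data analysis section is weak evidence. It belongs to the odds ratios, and a planning level for prevalence need not equal it. This stands: it is circumstantial support, and the arithmetic does not depend on it.

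Finally, the effect is small. No test, power statement or stopping rule hangs on the label, the result is not biased, and 184 is sufficient at 95%. That is true and limits the practical weight of the point. It does not make the stated claim correct.

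**Conclusion.** The concern holds. From the protocol's own inputs, 184 patients provide ±7 points at 95% confidence, not 97%. At 97% they provide about ±7.75 points, roughly 0.75 points wider on each side, and ±7 would need 226 patients. The most likely explanation is a 95% calculation labelled 97%.

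This rests on a two-sided normal-approximation interval, 7% read as absolute percentage points, a prevalence of 37.5% and no finite population correction. The other interval methods tried at 97% all need at least 221 patients, so the two-sided conclusion does not turn on the choice of method. The design itself is not undermined; the statement describing it is wrong in every place where it appears.

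**What to change.** The sponsor should first confirm the formula behind 184 and whether any source population size entered it. Then one of the following applies, made identically in the Abstract, the Synopsis and the Sample size section:

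- **Preferred:** replace 97% with 95%, keep N = 184 and ±7 points, and name the normal-approximation formula. This changes one number in three places and needs no extra patients; the only cost is a slightly less favourable stated confidence.
- **If 97% is intended with N = 184:** restate the accuracy as about ±7.75 points. This also needs no extra patients.
- **If 97% and ±7 points are both intended:** raise N to 226, at a cost of 42 more patients.
- **If a finite population correction was used:** state the correction and the population size, and say that the estimate refers to that population.

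Whichever is chosen, the interval reported with the prevalence should use the same confidence level. It would also be better to call the precision expected rather than guaranteed, since the realised margin depends on the observed prevalence and on the number of usable questionnaires.

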## Data analysis

The sample will be described in its clinical and demographic characteristics through descriptive statistical techniques. Continuous variables had been checked for normality with Shapiro Wilk test. Therefore, normally distributed data were expressed as mean and standard deviation (SD), and non-normally with median and first and third quartiles (q1-q3). Dichotomous variables, categorical variables, and scores were expressed as numbers and percentages.

Primary outcome was the prevalence of common psychiatric disorders in patients with T2D assessed through the Patient Health Questionnaire. Moreover, to evaluate potential risk/protective factors associated with patients’ psychiatric disorders positivity, we performed univariable logistic regression models. Therefore, for each factor, we calculated the Odds Ratio (OR) with 95% Confidence Interval (CI) of being positive to PHQ. Statistical analyses were performed with Stata software, and statistical significance cut-off was set p<0.05.

**The primary objective** will be achieved through the calculation of the prevalence of common psychiatric diseases in patients with T2D.

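### Associated factors are examined only through unadjusted, one-at-a-time odds ratios on a single PHQ-positive outcome; one short prespecified adjusted model should sit beside them.

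*Protocol*

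**What the plan says.** The protocol describes the factor analysis in two places, and they agree. Data analysis gives the purpose as "to evaluate potential risk/protective factors associated with patients’ psychiatric disorders positivity" and the method as "we performed univariable logistic regression models". The statistical analysis row of the Synopsis has "we will perform univariable logistic regression models". Each factor yields an odds ratio with a 95% interval "of being positive to PHQ", and "statistical significance cut-off was set p<0.05". Neither place names an adjusted model, a covariate list or a disorder-specific model.

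Materials and methods lists what the questionnaire covers: "major depressive disorder, other depressive disorders, panic attack disorder, other anxiety disorders, bulimia nervosa, binge eating disorder, dependence, or alcohol abuse". Data analysis treats positivity as one status, and Study procedures refers in the same way to those who test positive. The protocol never formally defines that status; positive for any listed disorder is the natural reading.

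The Synopsis gives no secondary objective. The factor analysis is additional to the primary prevalence estimate.

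**The concern.** There are two separate weaknesses.

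**No adjustment.** Demographic and clinical characteristics of diabetes outpatients can be expected to correlate with one another. A one-factor model gives each factor credit for whatever travels with it. A factor with no association of its own can reach p<0.05, and a reader has no adjusted figure to compare it with.

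**One outcome for several disorders.** A factor tied to depression but not to alcohol misuse appears diluted. A factor that acts in opposite directions on two disorders can appear to do nothing. The stated objective stresses disorders beyond depression, but the factor analysis as written does not distinguish them.

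What is at stake is how the list of associated factors will be read. The headline prevalence is not at stake.

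**Working it through.** **Inputs from the protocol (Sample size).** N = 184, expected prevalence 37.5%, half-width 7 points, stated confidence 97%.

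**The plan's own figure.** With n = z² p(1−p)/d², p = 0.375 and d = 0.07, 95% confidence gives 183.7, so 184; 97% gives 225.3, so 226. The 184 thus matches 95%, not 97%. That is a separate matter. I use 184 below because it is the planned number.

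**Is an adjusted model feasible?** Expected positives are 184 × 0.375 = 69, and expected negatives 115. At 10 events per parameter, 69/10 = 6.9, so 6 parameters. At 20 events per parameter, 69/20 = 3.45, so 3.

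**Confounding (assumed inputs).** Take a binary confounder present in half the patients, overall positivity 37.5%, and a factor with no effect given the confounder (true odds ratio 1). The factor is present in half of the patients overall, so 92 have it and 92 do not.

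*Strong case.* Confounder odds ratio 3; factor present in 80% of those with the confounder and 20% of those without.
- Positivity by confounder: 0.50 and 0.25 (mean 0.375; odds 1 and 1/3, ratio 3).
- With the factor: 0.8 × 0.50 + 0.2 × 0.25 = 0.45. Without it: 0.2 × 0.50 + 0.8 × 0.25 = 0.30.
- Crude odds ratio: (0.45/0.55)/(0.30/0.70) = 1.91.

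The other cases use the same steps. The last column is the two-proportion power at 92 per group.

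| Confounder OR | Factor prevalence, with / without confounder | Crude OR of the null factor | Chance of p<0.05 |
|---|---|---|---|
| 2 | 60% / 40% | 1.15 | 6.5% |
| 2 | 70% / 30% | 1.32 | 14% |
| 3 | 70% / 30% | 1.54 | 29% |
| 3 | 80% / 20% | 1.91 | 56% |

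**Pooling (assumed inputs).** Suppose depression or anxiety affects 20% of men and 33% of women, and alcohol disorder 15% and 3%, independently.
- Women versus men, depression or anxiety: (0.33/0.67)/(0.20/0.80) = 1.97.
- Women versus men, alcohol: (0.03/0.97)/(0.15/0.85) = 0.18.
- Any disorder: men 1 − 0.80 × 0.85 = 0.320; women 1 − 0.67 × 0.97 = 0.350.
- Pooled: (0.350/0.650)/(0.320/0.680) = 1.14.

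Two sizeable associations nearly cancel. Opposite directions are not needed for a loss. Take two independent groups at 20% and 21.9%, which combine to 1 − 0.80 × 0.781 = 37.5%. A factor with odds ratio 3 on the first and 1 on the second has a pooled odds ratio of 1.75.

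**Would separate models per disorder work?** The protocol gives no disorder-specific prevalence, so event counts cannot be derived. On the assumed alcohol rates and equal numbers of each sex, 184 × (0.15 + 0.03)/2 ≈ 17 events, enough for one parameter at 10 events each.

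**The case against.** The strongest reply is that this is a subsidiary, exploratory analysis and that crude odds ratios answer a legitimate question: who is more likely to screen positive. Confounding matters for claims of an independent effect, and the protocol speaks only of potential factors and of association. All of this stands, and it limits the weight of the point.

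Several stronger readings are tempting, and the protocol does not support them:
- *The odds ratios are confounded.* A reader might infer this, but no figure in the protocol shows it. Both the confounding and the pooling illustrations rest on assumed inputs. The supportable wording is unadjusted and open to confounding.
- *The screening service would be misdirected.* The Synopsis plans permanent screening for patients with T2D without selecting by factor, and Study procedures contacts all who test positive. No stated decision uses these odds ratios.
- *The plan makes a causal claim.* The risk/protective label leans that way for a cross-sectional survey, but the qualifiers potential and associated stand in the same sentence. At most this is a matter of labelling.
- *Each disorder needs its own regression.* Event counts may be far too small.

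It can also be said that a statistical analysis plan might add adjusted or disorder-specific results. It might. But the protocol names the method twice, and a plan that follows it would contain univariable models only. This is a stated choice rather than an omitted detail.

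**Conclusion.** The point holds at moderate weight. The protocol fixes unadjusted models as its only method for associated factors and, on the natural reading of an undefined term, applies them to one outcome that combines several kinds of disorder. The size of any bias is unknown. The range of 1.15 to 1.91 for a factor with no effect of its own, with about 6.5% to 56% of studies reaching p<0.05, depends entirely on the assumed confounder strength and imbalance. The near-cancellation to 1.14 depends on assumed sex-specific rates. What rests on the protocol's own figures is feasibility: 69 expected positives make a short adjusted model possible. The primary prevalence estimate does not depend on any of this.

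**What to change.** In Data analysis and in the matching Synopsis row:
1. Keep the univariable odds ratios and label them descriptive.
2. Add one prespecified multivariable logistic model on the pooled outcome, with at most about 6 parameters: age, sex and a few clinical variables. The protocol does not list what the information form collects, so choose only variables that it actually records. Do not select by univariable p-value.
3. Report crude and adjusted odds ratios side by side as exploratory associations.
4. State what counts as PHQ positive, and show factor distributions by disorder group, including alcohol, as descriptive tables rather than separate models.

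The cost is a few lines of text, one extra model and some tables, with no added patients. Adjusted intervals will be wider than the crude ones. If the information form records few clinical variables, the model will be correspondingly short and confounding by unrecorded factors will remain.
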